**Amendments (summarised on 18/11/2022):**

1. *Use of raw data of individual fatty acids rather than publicly deposited data of groups of fatty acids*. Following gaining access to full biomarker data in the MedLey trial, EPIC-InterAct investigators reconsidered the “biomarker score of clinical intervention assignment” (Protocol 1) as our primary approach to derivation of a biomarker score of the Mediterranean diet, as reported in the current manuscript. Prior to this, we viewed the use of groupings of fatty acids in the MedLey trial (as available in the publicly deposited dataset) for external application of the biomarker score to EPIC-InterAct as too strong a threat to validity of the analysis to consider this type of biomarker score as our primary approach, because the composition of individual fatty acids within such groupings may have been fundamentally different between the two studies.

2. *Use of logistic elastic-net regression modelling individual biomarkers and their first-order interactions rather than use of standard logistic regression with backwards selection of individual biomarkers*. We increasingly recognised the utility of elastic net regression to develop a model predicting a dependent variable with multiple correlated predictors. We also found the assumption of no interactions between biomarkers in the score to be severely violated and we allowed for selection of predictors among all pairwise biomarker interactions in addition to log-linear terms. Because of the need to consider a pool of predictor variables exceeding the number of participants following this amendment, we applied logistic elastic net regression as our primary method of variable selection in lieu of logistic regression with backwards selection based on minimising the Bayesian information criterion.

3. *Method of variable selection stabilisation.* In the logistic elastic net regression analysis, we exchanged the bootstrap-enhanced stability selection of biomarkers for stability selection with repeated cross-validation. We selected the former a priori based on our earlier experience of observational derivation of biomarker scores using linear models (Protocol 2). It did not identify any biomarker terms consistently predictive of randomised assignment in the MedLey trial despite selection of multiple biomarker terms in individual runs of elastic net regression models. Upon additional reading of the literature, we found that bootstrapping for classification problems is suboptimal and favours overly parsimonious models [15]. This issue would be reasonably expected to be exacerbated by performing variable stability selection across bootstrap samples, which is consistent with our lack of identification of biomarker predictors using the bootstrap-based stability selection approach.

4. *Omission of secondary analyses*. We considered several secondary analyses as being of little benefit for our inference and our final report and omitted them: 1) computation of net re-classification index in the MedLey trial; 2) computation of relevant reclassification indices in the EPIC-InterAct; 3) assessment of utility of the biomarker score over and above established risk factors for prediction of type 2 diabetes; and 4) longitudinal analyses for incident outcomes in the EPIC-Norfolk study. 1) In the MedLey trial, C-statistic was considered as satisfactory to evaluate the performance of the derived biomarker scores. 2) In EPIC-InterAct, “validation” of the biomarker score was considered invalid to assess by using self-reported dietary indices as the reference measure because of the measurement error in subjective reporting and potentially limited construct validity of the Mediterranean diet score. 3) To make the manuscript succinct and focused on the single research aim, we decided not to explore whether inclusion of the nutritional biomarkers would merit prediction of type 2 diabetes risk currently available in a clinical setting. Lastly, 4) the EPIC-Norfolk study is a part of EPIC-InterAct, ascertaining the incidence of a number of disease endpoints, not only type 2 diabetes (n diabetes cases = 681). For the purpose of simplicity and clear focus on type 2 diabetes as the primary outcome in the EPIC-InterAct (n cases = 9,453 in the current study), we decided to reserve any longitudinal analyses for multiple outcomes in the EPIC-Norfolk Study for future publications.

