**Brief description of studies:**

MedLey study is a two-arm parallel randomised controlled trial (RCT) of 137/166 (completed/enrolled) Australians aged ≥ 65 years [1]. Conducting a 6-month intervention, this RCT compared the effect of Mediterranean diet advice and provision of its key foods with the effect of a habitual diet on serum carotenoids, erythrocyte fatty acids and urinary electrolytes. As a measure of compliance to the intervention, self-reported adherence to Mediterranean diet was assessed using a 3-day weighed food diary at months 0, 2 and 4. Biomarkers were measured at months 0, 3 and 6. Raw data were made publicly available at: <https://doi.org/10.3390/nu9060534>.

EPIC-InterAct is a multi-country case-cohort study of type 2 diabetes nested within eight European countries of the European Prospective Investigation into Cancer Study (EPIC) [2]. EPIC-InterAct allows a large-scale epidemiological analysis of approximately twelve thousand incident cases of type 2 diabetes and sixteen thousand participants in the subcohort. Most participants had baseline measurements of plasma carotenoids and phospholipid fatty acids. Habitual diet was assessed using food frequency questionnaires (FFQ) or diet histories.

EPIC-Norfolk, one of the cohorts of EPIC, is a population-based cohort study in East of England [3]. Subsets of participants had baseline and follow-up measurements of plasma carotenoids, plasma phospholipid, and erythrocyte fatty acids, and 24-h and spot urinary sodium and potassium. Habitual diet was assessed at baseline and follow-up using FFQ and 7-day food diary.

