**Background:**

Ongoing work in EPIC-InterAct and EPIC-Norfolk aims to derive biomarker scores of habitual adherence to Mediterranean diet using combinations of circulating carotenoids, fatty acids and other nutritional biomarkers. Briefly, cross-validated penalised regression has been modelled to predict Mediterranean diet scores based on nutritional biomarkers. Mediterranean diet scores were calculated based on self-reported diet, using responses to country-specific instruments for dietary assessment. Linear combinations of all available biomarkers were considered, alongside models incorporating first order interactions between biomarkers. Both country-specific and subcohort-wide biomarker scores were developed.

Assessment of external validity of the biomarker scores in a trial setting is desirable. MedLey study dataset includes some of the biomarkers measured in EPIC-InterAct and EPIC-Norfolk which allows for such external validation. The table below shows the overlap between nutritional biomarkers measured in the three studies.

Development of a biomarker of intervention with Mediterranean diet is also of interest. Such a biomarker would have applications in assessment of adherence to the dietary intervention in a clinical setting as well as a non-clinical population-based setting. MedLey trial allows to assess whether or not a specific combination of nutritional biomarkers can differentiate between intervention with Mediterranean diet and habitual diet. The resultant classification model from MedLey trial can be examined for its external validity for a population-based setting by evaluating EPIC-InterAct and EPIC-Norfolk studies.

| **Table** Availability of nutritional biomarker data in MedLey trial and overlap with EPIC-Interact and EPIC-Norfolk studies | | |
| --- | --- | --- |
| MedLey | EPIC-InterAct | EPIC-Norfolk |
|  |  |  |
| **Serum carotenoids** | **Plasma carotenoids** | **Plasma carotenoids** |
| α-carotene, β-carotene, β-cryptoxanthin, lycopene, sum of lutein and zeaxanthin | all available | all available |
|  |  |  |
| **Erythrocyte fatty acids** | **Plasma phospholipid fatty acids** | **Plasma phospholipid and erythrocyte fatty acids** |
| total SFA | sum of individual SFAs | sum of individual SFAs |
| total TFA | sum of individual TFAs | sum of individual TFAs |
| MUFA-n9 | sum of individual MUFA-n9 | sum of individual MUFA-n9 |
| MUFA-n7 | C17:1 | sum of individual MUFA-n7 |

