**2. Biomarker score of clinical intervention assignment**

This analysis will aim to evaluate whether combinations of nutritional biomarkers can discriminate between the Mediterranean and habitual diet in MedLey trial at 6 months. We will adapt to a binary outcome the methods for evaluation of nutritional biomarkers established in the Women’s Health Initiative feeding trial [4].

Natural-log transformation will be applied to biomarkers to improve normality of distributions. Values outside of 25^th^ percentile minus 3 times the interquartile range (IQR) or 75^th^ percentile plus 3 times the IQR will be removed from the analysis. Logistic regression will be used to develop the biomarker score. Backward selection procedure based on Bayesian information criterion will be used to remove non-informative biomarkers. Multivariable fractional polynomial logistic regression will be used to evaluate the validity of fitting ln-transformed linear terms under log-linearity assumption. Any identified nonlinearities will be included in the logistic regression model. Assumption of no interactions between biomarkers will be evaluated using elastic net logistic regression with first order interactions between biomarkers. Bootstrap-enhanced stability selection will be used to identify consistently selected interactions [5]. Any interactions selected in ≥ 95% of bootstrap samples will be included in the logistic regression model.

Five-fold cross-validated C-statistic will be the primary measure of model performance. We will also calculate net reclassification index and sensitivity and specificity in a clinically relevant scenario.

The analyses will be undertaken using (i) full biomarker data, (ii) excluding urinary calcium and magnesium and (iii) excluding all urinary electrolytes. It will allow to assess the added value of 24-h urine collection to blood-based biomarkers and result in biomarker scores applicable to EPIC-Norfolk (ii) and EPIC-InterAct (iii).

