We will test whether the biomarker scores derived in MedLey trial can be used in EPIC-InterAct and EPIC-Norfolk (i) as a measure of degree of adherence to Mediterranean diet and (ii) to discriminate between high and low adherence to Mediterranean diet. The former aim will be addressed by linear regression of the trial-derived biomarker score and Mediterranean diet score based on dietary self-report. High and low adherence ranges will be defined by using the statistics in MedLey trial. To define the high adherence, we will use the median of the Mediterranean diet score +/- 1 point in the intervention group of MedLey trial. To define the low adherence, we will use the corresponding median +/- 1 point in the habitual diet group. Logistic regression and c-statistic will be used to evaluate discrimination between the two groups in EPIC studies. Net reclassification improvement will be estimated by analysing a predictive capability of the biomarker score in comparison to an intercept-only model and a multivariable-adjusted model including variables readily available in a clinical setting (age, sex, recruitment sites, and smoking status).

We will consider analysing prospective associations between the biomarker scores and type 2 diabetes (EPIC-InterAct) and cardiovascular endpoints (EPIC-Norfolk).

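### The primary score is trained on erythrocyte fatty acids and applied to plasma phospholipid fatty acids, and the documents specify no bridging between the two

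*Combined protocol and SAP*

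**What the plan says.** **Matrices.** Protocol 1, Brief description of studies, says that MedLey studied the "effect of a habitual diet on serum carotenoids, erythrocyte fatty acids and urinary electrolytes". For EPIC-InterAct it says: "Most participants had baseline measurements of plasma carotenoids and phospholipid fatty acids". The column headings of the overlap table in Protocol 1, Background, show the same difference. For EPIC-Norfolk that table has "Plasma phospholipid and erythrocyte fatty acids", and the study description says: "Subsets of participants had baseline and follow-up measurements of plasma carotenoids, plasma phospholipid, and erythrocyte fatty acids".

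**Pre-processing.** For the trial-derived score, Protocol 1, Statistical analysis plan, section 2, states: "Natural-log transformation will be applied to biomarkers to improve normality of distributions". It adds removal of values more than three interquartile ranges beyond the quartiles. The version without urinary electrolytes is the one meant for EPIC-InterAct.

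**Checks.** The planned check of the score as a measure of adherence in the EPIC studies is "linear regression of the trial-derived biomarker score and Mediterranean diet score based on dietary self-report", together with discrimination between high and low self-reported adherence.

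**Amendments.** Item 1 makes this score the primary approach once individual fatty acids are available. Grouped acids had been thought too weak "because the composition of individual fatty acids within such groupings may have been fundamentally different between the two studies". Item 2 moves to elastic net and allows all pairwise biomarker products alongside the log-linear terms.

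**The concern.** The exposure in an analysis of 9,453 diabetes cases (Amendments, item 4) uses weights learned in one sample matrix and values measured in another. The same fatty acid can differ between erythrocytes and plasma phospholipids in level, in spread and in response to diet. Item 1 deals with one threat to carrying the score across studies, the make-up of fatty-acid groups, and does not mention this second one. Unless the two matrices are aligned, the score tested against diabetes may not be the score that separated the trial arms.

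Nothing else in the plan would reveal the problem. The C-statistic in MedLey is computed in erythrocytes. The check in the EPIC studies is against self-reported diet; item 4 itself calls such validation in EPIC-InterAct invalid, and the additional amendment of 08/02/23 restores only the discrimination analysis.

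**Working it through.** The plan gives no cross-matrix correlation, level shift or scaling rule, so there is no figure of its own to reproduce. The check has three parts.

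**1. Is any bridging specified?**
- Protocol 1, section 2: ln-transform and outlier removal only. No within-study centring or scaling, cross-matrix calibration or restriction to concordant acids.
- Protocol 1, section 1: standardised differences are mentioned, but for EPIC-derived scores tested in MedLey.
- Protocol 2, Biomarker scores derivation: the only calibration formula maps questionnaire intakes to 24-hour recalls. EPIC fatty acids are expressed as mole percentages; no unit is given for MedLey.
- Amendments, items 1 to 4, and the additional amendment: the sample matrix is not mentioned.

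Result: none is specified.

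**2. What does a level shift do?** Let z1 and z2 be two ln-biomarkers on the training scale, and let the application matrix shift them by a1 and a2.
- Main terms only: β1(z1 + a1) + β2(z2 + a2) = β1·z1 + β2·z2 + constant. The ranking of participants and the hazard ratio do not change.
- With a product term: β12(z1 + a1)(z2 + a2) = β12·z1·z2 + **β12·a2·z1 + β12·a1·z2** + constant. The effective weight on z1 becomes β1 + β12·a2, and the weight on z2 becomes β2 + β12·a1.

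So after item 2 a pure level shift no longer cancels if the products are formed from uncentred values. This is algebra. It needs no assumed figure, but it does depend on the products being uncentred, which the documents leave open.

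A change of scale (z1 replaced by b1·z1) multiplies that biomarker's weight by b1 even in a main-terms score.

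**3. What does imperfect agreement do?** If the applied score has correlation ρ with the trained score, and the trained score is the relevant exposure, the log hazard ratio per SD is multiplied by ρ, so HR_seen = HR^ρ. Both ρ and the hazard ratio of 0.80 are assumed.

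| ρ (assumed) | HR seen |
|---|---|
| 0.5 | 0.80^0.5 = 0.89 |
| 0.8 | 0.80^0.8 = 0.84 |

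Centring and scaling leave ρ below 1 when the matrices agree imperfectly. For the product of two independent, centred biomarkers, each with cross-matrix correlation r, the product correlates r². With r = 0.5 that is 0.25. Products are therefore more exposed to poor agreement than main terms.

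**The case against.** **The documents are silent about conduct.** The amendments are a summary written to accompany a manuscript. Centring and scaling may have been done and not recorded. This stands: a reader might infer that the weights were in fact applied without bridging, but the documents show only that none is specified.

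**The matrices are disclosed, and item 1 claims less than it seems to.** The overlap table shows the difference openly. A reader might infer that item 1 declares individual acids a full solution. It says only why grouped acids had been thought too weak. The omission remains, because disclosing the difference does not bridge it.

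**Cross-matrix correlation is not itself the attenuation.** Both matrices are proxies for diet, and the score may also contain carotenoids. This stands, and it is why the figures of 0.89 and 0.84 are an illustration and not an estimate of bias.

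**EPIC-Norfolk may not supply a bridge.** It is tempting to read the plan as having paired samples at hand. The text speaks of subsets and does not say that the same people had both matrices at the same visit.

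**Within-study scaling is not neutral.** It removes true differences in diet level between the studies, and MedLey's spread at 6 months includes any contrast between the arms. It also cannot repair imperfect correlation, so it should not be presented as restoring the trained score. These limits should be reported with the result.

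**Conclusion.** The concern holds in this form: training and application use different fatty-acid matrices, the primary score admits product terms, and no bridging is specified. The mismatch and the silence are read directly from the text. The reweighting follows by algebra if uncentred ln-values are used. The direction and size of any effect on the diabetes hazard ratio cannot be computed from the documents. The range of 0.89 to 0.84 for an HR of 0.80 rests on an assumed score correlation of 0.5 to 0.8 and on treating the trained score as the relevant exposure. The documents do not support saying that the reported association is wrong, or that it is biased by a known amount. They do support asking for the scaling to be stated and for the result to be tested against the matrix difference.

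**What to change.** 1. **State and align the scale.** Centre and scale each ln-biomarker within study before forming products and applying the weights, and record this. It removes level and scale shifts. State that it does not remove imperfect correlation and that it also removes true between-study differences in level.
2. **Use EPIC-Norfolk if paired samples exist.** State whether any participants have both matrices. If so, report the erythrocyte–plasma phospholipid correlation for each acid in the score. Repeat the diabetes analysis, as a sensitivity analysis, with a score restricted to concordant acids or with values calibrated to the erythrocyte scale.
3. **Add a carotenoid-only score.** Refit it in MedLey and report its diabetes hazard ratio as a sensitivity analysis. Note that serum (MedLey) and plasma (EPIC) still differ, and that it is a different score, so a changed hazard ratio would not isolate the matrix effect.

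Do not re-derive the primary score by dropping acids below a correlation floor. Derivation was complete when the amendments were written, so the floor would be chosen after the results were known.

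If there are no paired samples, steps 1 and 3 remain. The cost is extra analysis on existing data; no new measurements are needed.

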**Additional amendment (08/02/23):**

Because of a request in the peer-review process, we have now performed the analysis of discriminatory performance of the biomarker score for high versus low self-reported adherence to the Mediterranean diet. This analysis was previously omitted as described under point four of the above section “Amendments (summarised on 18/11/2022).”

